**Figure 2 F2:**
[figure not shown]
Description of technique for measuring the h-PSV deceleration time in SMA. The PSV was 83.3 cm/s and the h-PSV was 41.7 cm/s. The horizontal dotted line indicates the h-PSV deceleration time (153 ms).

#### MCA

3.4.1B.

The MCA travels laterally and enters the sylvian fissure and is the largest branch of the internal carotid artery supplying the basal ganglia, parietal and temporal lobes. The course of the artery makes it ideal for Doppler assessment. A sectoral transducer 8–12 MHz will be used and placed superior and parallel to the zygomatic arch with the marker directed anteriorly. The colour Doppler will be used, tilting or sliding the probe gently to identify the circle of Willis, with importance to set the colour scale low (10–20 cm/s). The MCA is seen coming directly forward. The PW Doppler cursor will be placed in the proximal portion of the MCA to obtain the velocity profile.

#### ACA

3.4.2B.

The ACA runs in the longitudinal fissure and curves around the genu of corpus callosum supplying the basal ganglia, frontal and parietal lobes. The transducer will be placed in the fontanelle in the midline with the marker directed anteriorly. The ACA will be identified using the colour box, with importance to set the colour scale low (10–20 cm/s). The Power Doppler cursor will be placed in the distal portion of the ACA in order to obtain the velocity profile.

#### SMA

3.4.3B.

The superior mesenteric artery (SMA) is the second artery arising from the abdominal aorta. The SMA supplies nearly the entire small intestine and a substantial part of large intestine. The transducer with a lower frequency of 5–8 MHz will be used, placed below the xiphoid process with the probe marker directed superiorly. A 2D image will be used to find the abdominal aorta and colour Doppler will be used to identify the celiac trunk flow and the SMA flow directed forward, but at an angle. The PW Doppler cursor will be placed in the SMA, sliding and tilting the probe to decrease the angle of insonation and to obtain the velocity profile. The SMA measurement will be performed fasting, prior to the next feeding.

#### RRA

3.4.4B.

A transducer with a lower frequency of 5–8 MHz was used. The transducer will be placed on the flank a few centimetres above the level of the umbilicus, the probe marker directed superiorly. The kidney will be identified in the long axis on 2D imaging. Blood flow from the aorta to the renal hilum will be found using Colour Doppler and the PW Doppler cursor will be placed in the RA prior to the point in which it branches in the renal hilum, sliding and tilting the probe to decrease the angle of insonation and to obtain the velocity profile.

In order to assess the repeatability of the measurements, a pairwise comparison will be made between the results of 2 series of measurements performed by one researcher ([name]) (intra-observer variability) and two researchers ([name] and [name]) (interobserver variability). On the basis of these series of measurements, the value of the Pearson linear correlation coefficient (*R*) will be determined—as an indirect measure of the impact of random variability on the measurement results and the coefficient of variation (*V*) defined as the quotient of the mean of the squared differences between the pairs of measurements to the product of the standard deviations of both series of measurements. This method of calculating the coefficient of variation provides for taking into account the systematic error component.

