### Study population

3.3.

The study will include 100 neonates (50 subjects and 50 controls).
•Neonates with gestational age ≥35, who experienced an episode of perinatal ischaemia and who were qualified for hypothermia treatment according to the Standards of Medical care of Neonates in Poland will be enrolled to the subject group (T) (Table 5)•Healthy, term neonates, who underwent echocardiography on days 3–7 of life (after closure of ductus arteriosus, or with trace, insignificant haemodynamic ductus arteriosus) for reasons such as difficult adaptation, gestational diabetes of the mother etc.

**Table 5 T5:** Indications for hypothermic treatment according to the standards of medical care of neonates in Poland 2021 (3).

Indications for TH		
Criteria Group A. Neonates born at ≥35 weeks of gestation, who experienced a period of hypoxia and at at least one of the factors in each of the sub-groups		Group B-neurological criteria. Neonates fullfilling the criteria of group with A with fluctuating states of consciousness who has at least one of the following factors:
Sub-group 1	Sub-group 2	– Hypotonia – Abnormal response to stimuli, including abnormal occulomoor or pupillary reflexes – Absent or weak sucking reflex – Clinically confirmed convulsions
– Apgar score ≤5 week 1, 3, 5, 10 min after birth – Continuous resuscitation with tracheal or mask withinn 10 min after birth	– Cord blood or blood pH within 1 h of life ≤7, however, with specicif assesment of pH results in the region of 7.01–7.15 – A BE base deficiency of at least 16 mmol/l cord blood or other samoles samples within 60 min after birth.	

Enrolment of patients will be based on patient medical records. Physicians responsible for recruitment of patients will gather additional information associated with the inclusion and exclusion criteria (Table 6) through detailed history, taking into account the clinical condition of patients and the results of tests. The study procedure will be explained to patient's guardians who will also receive an information leaflet. Guardians will then be asked to provide two copies of informed consent. Consent forms and information papers will be provided solely in the Polish language.

**Table 6 T6:** Inclusion and exclusion criteria.

Inclusion criteria (subjects)	Exclusion criteria

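### The coefficient of variation V planned for repeatability is not a coefficient of variation, and both V and Pearson's R mix measurement error with the spread between infants

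*Protocol article*

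**What the plan says.** The closing paragraph of section 3.4.4B of the protocol article sets out the repeatability check. For intra-observer variability, "a pairwise comparison will be made between the results of 2 series of measurements performed by one researcher"; for inter-observer variability, the two series come from two researchers.

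Two indices are fixed:

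- Pearson's R, described "as an indirect measure of the impact of random variability on the measurement results".
- A coefficient of variation V, given by "the quotient of the mean of the squared differences between the pairs of measurements to the product of the standard deviations of both series". The reason given for this form is that it "provides for taking into account the systematic error component".

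The paragraph sets no acceptance threshold for R or V. It does not say which infants, or how many, enter the repeatability series. Section 3.3 gives the population from which they could come: "The study will include 100 neonates (50 subjects and 50 controls", that is, cooled infants and healthy term controls.

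**The concern.** A coefficient of variation is an SD divided by a mean. V as written is a mean square divided by a product of two SDs, and no mean appears in it. The article does not leave this definition to another document; it writes the formula out, and the formula does not match the name.

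The denominator matters more than the name. The SD of each series is mostly the spread between infants. R and V therefore both compare measurement error with how different the infants happen to be, and a more varied set of clips improves both with no gain in precision.

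The outcomes in section 5 rest on the echocardiographic and Doppler parameters grouped in section 3.5. To judge whether a difference between cooling and warming, or between cooled infants and controls, exceeds measurement noise, a reader needs the error in units or as a percentage of the mean. Neither planned index gives that.

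**Working it through.** The article states no repeatability figure, so there is nothing to reproduce. The formula comes from section 3.4.4B. All means, SDs and CVs below are illustrative assumptions, because the article gives none.

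**1. What V is.** Let d be the paired difference, s1 and s2 the SDs of the two series, and bias the mean of d. Then

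mean(d²) = bias² + s1² + s2² − 2R·s1·s2,

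and dividing by s1·s2 gives

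V = bias²/(s1·s2) + s1/s2 + s2/s1 − 2R.

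A check on simulated pairs gave 0.37318 on both sides. With equal SDs (s1 = s2 = s), V = 2(1−R) + (bias/s)². If there is also no bias, V is R restated.

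**2. Same error, different spread.** Let w be the within-infant error SD and B the between-infant SD, both as fractions of the mean, with no bias. Then R = B²/(B²+w²) and V = 2w²/(B²+w²). For w = 0.05:

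| B | R | V |
|---|---|---|
| 0.10 | 0.0100/0.0125 = 0.80 | 0.005/0.0125 = 0.40 |
| 0.20 | 0.0400/0.0425 = 0.94 | 0.005/0.0425 = 0.118 |
| 0.30 | 0.0900/0.0925 = 0.97 | 0.005/0.0925 = 0.054 |

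The within-subject CV is 5% in every row, yet V falls about sevenfold (0.40/0.054 = 7.4).

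**3. Different error, same V.** With w = 0.10 and B = 0.30, V = 0.02/0.10 = 0.20. With w = 0.15 and B = 0.45, V = 0.045/0.225 = 0.20. A 10% and a 15% error cannot be told apart.

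**4. V against a true CV.** Take a mean of 0.40, error SD 0.03 and between-infant SD 0.08. V = 2(0.0009)/(0.0064+0.0009) = 0.247, while the within-subject CV is 0.03/0.40 = 7.5%. Doubling the mean to 0.80 halves the CV to 3.8% and leaves V at 0.247. Taking the square root does not help: √0.247 = 0.497.

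**5. V does respond to error and to bias.** At between-infant SD 0.08 without bias, error SDs of 0.015, 0.03 and 0.06 give V = 0.068, 0.247 and 0.720. At error SD 0.03, biases of 0, 0.03 and 0.08 give V = 0.247, 0.370 and 1.123, while R stays at 0.877.

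**6. A pure offset.** Suppose the second reader reads exactly 20% high with no random error. Then R = 1.00 and V = 0.04(1+B²)/(1.2B²), which is 3.37, 0.87 and 0.40 for B = 0.10, 0.20 and 0.30. V flags the offset, but its size again depends on the spread.

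**7. The proposed replacement.** The within-subject CV is √(mean(d²)/2)/mean. With mean 0.40, error SD 0.03 and no bias, it stays at 7.5% for between-infant SDs of 0.04, 0.08 and 0.16, while V runs through 0.720, 0.247 and 0.068. In a simulation with 50 pairs and 5,000 runs it averaged 7.5% at all three, while V averaged 0.739, 0.256 and 0.071. The half-width of the 95% limits of agreement is 1.96 × √2 × 0.03 = 0.083 throughout. Biases of 0.03 and 0.08 raise the within-subject CV to √(0.0009+0.00045)/0.40 = 9.2% and √(0.0009+0.0032)/0.40 = 16.0%, so systematic error is still counted.

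**The case against.** The strongest defence is that V is a defined, reproducible ratio of error to spread under a poor name. Several parts of that defence stand.

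- A reader might infer that R and V reflect spread between infants instead of measurement error. They do not. The error term is in the numerator of V, and step 5 shows both random error and bias moving it.
- A reader might infer from R = 1.00 under a pure offset that the plan is blind to bias. The article claims only that R reflects random variability, indirectly, and it adds V to cover systematic error. Step 6 shows that V does so, and the article's sentence on this is correct.
- A reader might infer that parameters will be passed or failed on R or V. No criterion is stated. Nor does the article present V as a percentage.
- Pooling cooled infants with controls in the repeatability series is possible but is not stated.
- An ICC would not cure the problem. Without bias and with equal SDs it equals R, so V = 2(1−ICC), and it varies with spread in the same way.

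The defence does not answer two things: the name does not fit the formula, and neither index separates error from spread or gives it on a usable scale.

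**Conclusion.** The point holds as a matter of measurement reporting. V is mislabelled, it repeats R when there is no bias and the SDs are equal, and R and V both confound error with between-infant spread. The algebra holds for any data. The sizes, such as V = 0.40, 0.12 or 0.05 for the same 5% error, rest on assumed CVs and would differ by parameter.

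The documents do not support a claim that the main results are compromised. R and V enter neither the comparisons in section 5 nor the power calculation in section 9. Followed as written, the plan would publish repeatability figures that cannot be read as percentage error or compared between parameters or series with different spread.

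**What to change.** For each parameter, and separately for the intra- and inter-observer series:

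- Replace V by the within-subject CV, √(mean(d²)/2)/mean. It uses the same squared differences and keeps the article's aim of including systematic error.
- Report the Bland–Altman mean difference with 95% limits of agreement, which shows bias and random error separately and in units.
- Keep R, or an ICC, only as a supplementary index, described as dependent on spread.
- State which infants enter the repeatability series.

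The cost is a change of analysis wording. The planned duplicate readings are enough, and no further scans, readings or staff are needed.

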### The authors classified the parameters into the following groups depending on the evaluation of the function.

3.5.

•LV function: global LV function-MPI (PD, TDI), systolic function-FS%, LVO, *S*′, MAPSE, diastolic function-*E*:*A* ratio, *E*′:*A*′ ratio measured on MV.•RV function: global RV function-MPI (PD,TDI), systolic function: *S*′, TAPSE, diastolic function-*E*:*A* ratio, *E*':*A*′ ratio measured on TV**.**•PPHN: AcT:RVET, TAPSE, incompetence gradient rTV + right atrium pressure•Systemic Flow (50%): SVCO•Systemic resistance: h-PSV-half peak systolic velocity, RI-resistance index in SMA, ACA, MCA, RRA

### Strengths of the study

3.6.

To assess the hemodynamics of the circulatory system, the authors also used echocardiographic measurements, the value of which is independent of the presence of DA, PFO, HR, age, body weight, such as the TEI index for RV and LV, and used the tissue Doppler function to assess the myocardium.

An additional advantage of the study is the large size of the study group compared to other publications.

## Treatment or intervention

4.

No study-related interventions are planned. All neonates will be treated according to current guidelines.

## Study outcomes

5.

5.1.

•Assessment of the influence of TH on systolic-diastolic functions of the left and right ventricles in comparison with the control group•Assessment of the effect of the warming phase on the systolic-diastolic functions of the left and right ventricles in comparison with the control group

5.2.

•Assessment of the influence of TH on the cerebral, visceral and renal circulation in comparison with the control group•Assessment of the effect of the warming phase on the cerebral, visceral and renal circulation in comparison with the control group

This study assesses the hemodynamic changes by means of echocardiographic Doppler examination in neonates with HIE during TH in the warming phase in comparison with the control group of healthy neonates.

The intention is to assess the impact of TH on the cardiovascular system, including the cerebral, visceral and renal circulation.

TH may have an adverse effect on the cerebral circulation by increasing vascular resistance and loss of adaptation of the cerebral vessels, which in turn can lead to hypoperfusion of vital organs.

The effect of the warming phase on the cardiovascular system by increasing heart rate and improving cardiac output will also be carefully examined. The assumption is that the changes in blood pressure (systolic/diastolic) have a decisive impact on the metabolism of drugs, including vasopressors/inotropics, which in turn affects their choice and fluid therapy.

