### Impact of hypoxia on the cardiovascular system

1.1.

Transitory hypoxia of the myocardium (and its resultant dysfunction), which may, but not necessarily, present clinically, occurs in two thirds of neonates born with perinatal asphyxia (1). There is no doubt that that this is one of the more frequent cause of circulatory insufficiency. Both an episode of ischaemic hypoxia in the perinatal period and the changes in the distribution of blood may lead to diminished perfusion of the cardiac muscle. An additional but no less important impact on cardiac function is the immaturity of the neonatal myocardium and its reduced contractility secondary to acidosis and hypoxia. Ischaemia and acidosis lead to imbalance in favour of production of endothelin 1, which leads to reduced production of nitric oxide and vasoconstriction of pulmonary vessels and therefore greater PVR which has a detrimental effect on the already impaired right ventricular (RV) function. The weak RV function and increase PVR impair filling and function of the LV and thus, they can affect systemic and cerebral blood flow (2, 3).

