### Study design

3.1.

This is a multicentre, prospective, case-control, observational study. The number of subjects under observation will be 100 neonates (study summery Tables 2, 3). The enrolment, intervention and assessment schedule is presented in Table 4. Initial echocardiography and cerebral and abdominal ultrasonography will be conducted according to physician recommendation on day 1/2 after birth—hypothermia group echo1 (T1) with repeat examination on conclusion of hypothermia, during warming i.e., on day 4/7 of life—hypothermia group echo2 (T2). In view of the need for cooling of the neonate from the first hour of life there is no possibility to conduct theses examinations prior to introducing hypothermia.

**Table 2 T2:** Study summary.

Title	Echocardiographic and Ultrasound Evaluation of Haemodynamic Parameters in Hypoxic Neonates Treated With Hypothermia.	
Methodology	Multi-centre, prospective, case-control, observational study.	
Study duration	The study will take place from June 2021—June 2023	
Study Centre(s)	Neonatal Clinic and Neonatal Intensive Care unit, Warsaw Medical University [name]	
	ŻELAZNA Medical Center Ltd St. Sophia's Specialist Hospital Medical Centre Department of Prematurity and Neonatal Pathology	
Objectives	**Primary objectives**:	
	Assessment of contraction-relaxation function of the left and right ventricle during therapeutic hypothermia and warming period.	

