## Monitoring and harms

10.

The research is observational and non-interventional. Echocardiography and ultrasound examination of the cerebral and renal circulation is an essential diagnostic tool in neonates treated with TH and will not otherwise disrupt the diagnostic and therapeutic process of the neonate. Biological material—will not be collected for the purposes of the study.

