## Implications for practice

12.

The effect of TH and the warming phase on the cardiovascular system, including cerebral, visceral and renal circulation will be determined. The intention is to attempt to show the impact of each phase on the metabolism of drugs, including vasopressor/inotropic drugs, which in turn affects the choice and fluid therapy.

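### The outcomes in Section 5 name the difference between cooled HIE neonates and healthy controls as the influence of TH and of warming, but that comparison cannot isolate either

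*Protocol article*

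**What the plan says.** Section 5 (Study outcomes) lists under 5.1 "Assessment of the influence of TH on systolic-diastolic functions of the left and right ventricles in comparison with the control group" and under 5.2 "Assessment of the influence of TH on the cerebral, visceral and renal circulation in comparison with the control group". Each has a parallel item for the effect of the warming phase, also read against controls. Table 3 (what the study adds) and Section 12 repeat the causal claim, saying that the impact or effect of TH and warming will be determined.

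The groups are defined in Section 3.3. Cases have had perinatal ischaemia and qualify for cooling. Controls are "Healthy, term neonates, who underwent echocardiography on days 3–7 of life", with the duct closed or of no haemodynamic importance; Section 5 likewise places the comparison "in comparison with the control group of healthy neonates". Cases are scanned on day 1/2 during cooling (T1) and on day 4/7 during warming (T2). Controls are scanned once (N). Section 3.1 explains that "there is no possibility to conduct theses examinations prior to introducing hypothermia".

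Section 1.1 says that transient myocardial hypoxia, with the dysfunction it causes, "occurs in two thirds of neonates born with perinatal asphyxia". The limitations in Table 3 name drugs, ventilation, thrombotic changes and transitional shunts. They do not name asphyxia itself or the different age at T1 and at the control scan.

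On drugs, Section 12 states: "The intention is to attempt to show the impact of each phase on the metabolism of drugs". Section 7 lists the need for drugs, their type and their dose. Section 10 says that biological material "will not be collected for the purposes of the study".

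**The concern.** The outcome wording attaches one cause to a contrast in which several causes move together. By the protocol's own account, asphyxia and TH act on the same measurements in the same direction: Section 1.1 gives asphyxia raised pulmonary vascular resistance, impaired right ventricular function and poorer left ventricular filling, and Section 1.2 gives TH the same sequence. Section 1.2 also notes that randomised trials found no increased risk of persistent pulmonary hypertension with TH. Even so, a case-control difference in the markers that Section 3.5 groups under pulmonary hypertension would count here as an influence of TH.

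Section 1.2 describes TH as standard of care. A reader who takes the outcome label at face value could attribute to that treatment what belongs to the injury it treats.

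**Working it through.** There is no plan figure to reproduce. Section 9 gives the form of an F-test power calculation but no significance level, power, effect size or standard deviation, and the point does not depend on the sample size. The check is to set out what each group carries.

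| Scan | Asphyxia/HIE | Temperature phase | Intensive-care treatment | Age at scan |
|---|---|---|---|---|
| T1 | yes | cooling | as needed | day 1/2 |
| T2 | yes | warming | as needed | day 4/7 |
| N | no | never cooled | not expected (healthy) | days 3–7, duct closed or insignificant |

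**Step 1: what each contrast contains.**
- T1 − N = TH + asphyxia + treatment + postnatal age and transitional circulation.
- T2 − N = warming + residual asphyxia effects + treatment.
- T2 − T1, within infant = change from cooling to warming + recovery over time + age + change in treatment. The infant and the original insult are held constant.

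**Step 2: can the parts be separated?** Code HIE and TH as 0/1. Cases are (1, 1) and controls (0, 0), so the two columns are identical and only the sum of the two effects can be estimated. Suppose the observed difference were 0.6 SD. Leaving the other components aside, these splits fit equally well:
- asphyxia 0.6, TH 0;
- asphyxia 0, TH 0.6;
- asphyxia 0.9, TH −0.3.

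A covariate cannot help, because no infant has one exposure without the other, and no pre-cooling scan supplies a baseline.

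**Step 3: how readily would a difference appear with no TH effect?** Inputs: 50 cases and 50 controls (Section 3.3), and the F test of Section 9 with k = 2 and N = 100. The two-sided 5% level and the range of asphyxia effects d (in SD) are assumptions. The noncentrality is λ = N(d/2)².

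| Asphyxia effect d, TH effect 0 | λ | Probability of significance, one parameter |
|---|---|---|
| 0.2 | 100 × 0.1² = 1 | 0.17 |
| 0.5 | 100 × 0.25² = 6.25 | 0.70 |
| 0.6 | 100 × 0.3² = 9 | 0.84 |
| 0.8 | 100 × 0.4² = 16 | 0.98 |

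Because λ grows with N, a larger study makes such a result more likely and leaves the ambiguity where it was.

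**Step 4: drug metabolism.** An effect on metabolism needs a concentration or a clearance. Section 7 lists neither, and Section 10 rules out samples taken for the study. Section 5 treats the link between blood pressure and drug metabolism as an assumption, whereas Section 12 intends to show an impact of each phase on it. Recorded doses describe use, not metabolism.

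**The case against.** The strongest reply is that the governing objectives in Section 2 are descriptive: function during cooling and warming, and circulation in neonates and controls. Section 5 itself restates the study in nearly those terms. The design constraints are also disclosed: a scan before cooling is not possible, and an uncooled HIE group is hard to justify where cooling is standard of care. All of this stands, and it shows that the design is legitimate as description. It does not rescue the outcome items, which name TH and warming as the cause, nor the limitations, which omit asphyxia. A separate analysis plan could not repair this, because the confounding lies in the groups.

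Controls scanned for difficult adaptation or maternal diabetes are only loosely healthy, but they still represent neither HIE nor TH.

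A reader might also infer stronger points that the documents do not support:
- *That the study holds no informative contrast.* T1 and T2 are planned in the same infant, with internal temperature recorded at each scan. That contrast is useful, though mixed with recovery and age.
- *That T1–T2 must become the main comparison.* This is partly a preference, and its place may be settled in an analysis plan that is not shown.
- *That drug metabolism is a failed objective.* It is neither an objective nor a listed outcome. Section 12 puts it as an intention to attempt, under implications for practice.
- *That drugs and ventilation are recorded only over the whole stay.* Table 4 marks medication across days 0–30, but a condensed article need not show the timing of each form entry.

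**Conclusion.** The outcome wording is wrong for the comparison it describes. Neither T1 − N nor T2 − N isolates TH or warming. The share of either difference due to TH or warming is not identifiable at any sample size, so the size of the error cannot be stated. The probabilities of 0.17 to 0.98 only illustrate how readily asphyxia alone could produce a significant result; they rest on the assumed 5% level and on assumed asphyxia effects of 0.2 to 0.8 SD. The conclusion itself needs no numerical assumption. It follows from the group definitions, the scan times and the absence of a pre-cooling scan.

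This does not make the study uninformative, and it does not mean that a future report must misattribute the findings. The fault lies in the label on the outcomes and in what the limitations omit. The drug-metabolism statement is a secondary, smaller fault of the same kind: a conclusion with no data item behind it.

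**What to change.** 1. Reword 5.1 and 5.2 as the difference between cooled neonates with HIE (during cooling; during warming) and healthy neonates, in line with the objectives in Section 2. Bring the matching sentences in Table 3 and Section 12 into agreement.
2. Add two limitations to Table 3: asphyxia itself, which coincides with TH in every case; and the difference in postnatal age and ductal status between T1 and the control scan.
3. Report the within-infant T1–T2 change alongside, with the recorded core temperature. Describe it as change from cooling to warming including recovery over time, not as a pure effect of TH or of warming.
4. Delete the drug-metabolism intention in Section 12, or replace it with a description of recorded vasoactive drug use by phase. Keep the related sentence in Section 5 as a background assumption only.

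The cost is a change of wording and a more modest claim. No new patients, scans or samples are needed.

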## Objectives

2.

Haemodynamic changes were assessed by echocardiography doppler in neonates with HIE during TH and the warming phase.

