### Primary objectives

2.1.

Assessment of left and right ventricular systolic-diastolic function during therapeutic hypothermia and in the warming phase.

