**Limitations**
• Cardiovascular haemodynamics during TH may also be disturbed by the administration of inotropic, anticonvulsant sedative agents as well as mechanical ventilation or thrombotic changes.
• The specificity of the transient circulation (presence of patent ductus arteriosus, patent foramen ovale) may interfere with some echocardiographic measurements, such as CO (Cardiac output) for LV (left ventricle) and RV (right ventricle).

**Table 4 T4:** Proposed schedule of enrolment.

Study plan	Birth	1–2 days	3–7 days	0–30 days*
Anthropometry	X			
Medical history collection	X			X
Enrolment	X			
Eligibility assessment		X		
Medication (inotropics, sedatives, anticonvulsants)				X
Ultrasound of brain				X
MRI brain				X
Echocardiography		X^1^	X^2^	

X^1^–1 echo for group T (T1), X^2^–2 echo for group T (T2) and echo in group *N* (*N*).

* Entire observation period.

Images and clips from examinations conducted for indications, other than hypothermia, most frequently because of difficult adaptation, will be used for neonates in the control group (*N*). The study will take place in the period June 2021–June 2023. The proposed protocol of the study is shown in Figure 1.

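### The outcomes called the effect of the warming phase compare infants with healthy controls; on their own they cannot show whether function changed on warming, and the within-infant T2 minus T1 change is not a named outcome

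*Protocol article*

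**What the plan says.** - **Outcomes.** Section 5.1 gives one bullet for TH and one for warming, both against controls. The warming bullet is "Assessment of the effect of the warming phase on the systolic-diastolic functions of the left and right ventricles in comparison with the control group". Section 5.2 repeats the pattern: "Assessment of the effect of the warming phase on the cerebral, visceral and renal circulation in comparison with the control group".
- **Objectives.** The opening of section 2 reads "Haemodynamic changes were assessed by echocardiography doppler in neonates with HIE during TH and the warming phase". The primary objective (2.1) is "Assessment of left and right ventricular systolic-diastolic function during therapeutic hypothermia and in the warming phase" and names no control group. The secondary objectives (2.2) do name controls.
- **Expected effect of warming.** Section 5 adds: "The effect of the warming phase on the cardiovascular system by increasing heart rate and improving cardiac output will also be carefully examined".
- **Scans.** Group T is scanned on day 1/2 (T1), "with repeat examination on conclusion of hypothermia, during warming i.e., on day 4/7 of life" (T2). The note to Table 4 places the single control scan in the T2 column: "2 echo for group T (T2) and echo in group" N. Section 3.3 describes the controls as healthy term neonates scanned on days 3–7.
- **Analysis.** Section 9 describes a one-factor F test for equality of k means with N–k degrees of freedom. It does not state k and contains no paired or repeated-measures element.

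**The concern.** The objectives and the text of section 5 describe warming as something that moves an infant from one state to another: heart rate rises and output improves. That is a change from T1. The outcome carrying the name of the warming effect measures something else, namely how far asphyxiated, cooled infants differ from healthy ones at the time of the second scan.

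That distance mixes what happened between the scans with whatever deficit was present at T1. It can be zero when function changed a great deal and large when function did not change at all. The contrast that separates these cases, with each infant as its own control, is collected by design but is not a named outcome. At stake is whether the study can make a tested statement about change on warming, which belongs to its primary objective.

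**Working it through.** **1. Which contrast the bullet allows.** Each control has one echo, in the T2 window, and no day 1/2 scan. The only comparison of the warming phase with controls is therefore T2 against N.

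**2. What that contrast contains.** In means:

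T2 − N = (T2 − T1) + (T1 − N)

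Let controls be 0 and T1 be −0.5 SD (assumed).
- Full recovery, T2 = 0: T2 − N = 0.5 + (−0.5) = 0. The change was 0.5 SD.
- No change, T2 = −0.5: T2 − N = 0 + (−0.5) = −0.5 SD. The change was 0.

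**3. How often each test is significant.** Inputs: 50 infants per group (sections 3.1 and 3.3). Assumed, because the article gives no values: two-sided alpha 0.05, unit SD, within-infant correlation ρ of 0.3, 0.5 or 0.7, and all 50 infants with both scans. 10,000 simulated studies per setting:

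| True pattern | T2 v N | Paired T2 − T1 (ρ = 0.3 / 0.5 / 0.7) |
|---|---|---|
| Full recovery (−0.5 to 0) | 5% | 83% / 93% / 99% |
| Half recovery (−0.5 to −0.25) | 23–24% | 31% / 41% / 61% |
| No change (−0.5 to −0.5) | 69–70% | 5% / 5% / 5% |

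T2 against N is behaving correctly as a test of residual difference. It is simply not a test of change.

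**4. Whether the section 9 test supplies the change.** If k = 3 (T1, T2, N), the alternative hypothesis includes T1 differing from T2. But N–k degrees of freedom treat the two scans of one infant as if they came from different infants. An unpaired T2-against-T1 comparison in the same simulation gave 74–82% under full recovery, against 83–99% paired. Under no change its error rate was 0–2% instead of 5%.

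**5. Precision, for illustration.** At 80% power and two-sided alpha 0.05:
- T2 v N, 50 v 50, 98 df: non-centrality = d × √(50/2) = 5d. The required value is 2.83, so d = 2.83 / 5 = 0.57 SD.
- Paired, n = 50, 49 df: non-centrality = d × √50 / √(2(1 − ρ)). The required value is about 2.86, so d = 0.404 × √(2(1 − ρ)). For ρ = 0.3, 0.404 × 1.183 = 0.48 SD. For ρ = 0.5, 0.404 × 1 = 0.40 SD. For ρ = 0.7, 0.404 × 0.775 = 0.31 SD.

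These detectable differences belong to two different questions. They show that the paired contrast is feasible with the planned number, not that one estimate should replace the other. The planned total of 100 cannot be reproduced from the article, since alpha, power, effect size, SD and k are not given; the point does not depend on it.

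**The case against.** The strongest reply is that the authors plainly intend to look at change: section 2 speaks of changes, section 5 says the rise in heart rate and output will be examined, and the same infants are rescanned. The F test may have three levels, and a full analysis plan may specify a paired model. That stands as far as intent goes. A reader might infer that the plan excludes any T1-to-T2 comparison, and the documents do not support that. What remains is that the named outcome uses the control comparator and that the only test described does not take account of the pairing.

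A reader might also infer that full recovery would be reported as no effect of warming. That goes too far. The TH and warming bullets would be read together, and a depressed T1 beside a normal T2 would look like recovery. Even so, setting two separate results against controls side by side does not test the change.

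A third tempting step is to size the problem from the LVO reduction in Table 1. That entry has no stated reference group, so it cannot be equated with T1 − N and is not used here.

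Finally, T2 − T1 does not isolate warming either. It spans day 1/2 to day 4/7 and includes postnatal transition, recovery from hypoxia and changes in drugs and ventilation. The limitations in Table 3 list transitional circulation and support as disturbing factors. Controls have no day 1/2 scan to separate these, whereas T2 and N are close in age. This objection stands in full. It is why T2 v N should stay and why the change should not be called the effect of warming. Section 2.2 and Table 3 also show that comparison with controls is wanted, especially for 5.2.

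**Conclusion.** The point holds as a mismatch between label and contrast. In 5.1 and 5.2 the effect of the warming phase is a comparison with healthy controls, which carries the T1 deficit and cannot by itself show whether function changed. With an assumed 0.5 SD deficit and 50 per group, it is significant in 5% of studies when function recovers fully and in about 69% when nothing changes. The paired contrast gives 83–99% and 5% for assumed correlations of 0.3 to 0.7.

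The identity in step 2 needs no assumptions; the percentages and detectable differences do, and are illustrative. The finding concerns the stated comparator, not missing analysis detail. A paired analysis in a fuller plan would help, but the outcome as worded would still carry the wrong name. It does not follow that the control comparison is wrong or should be dropped.

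**What to change.** 1. In 5.1, add a named outcome: the within-infant change T2 minus T1 in group T, analysed by a paired or mixed model and described as *change over the warming period*.
2. In 5.2, add the same outcome beside the control comparison that the secondary objectives intend.
3. Keep T2 against N in both places, relabelled *residual difference from healthy neonates during warming*.
4. In section 9, state k and say that T1 and T2 come from the same infants and are analysed accordingly.
5. Add to the limitations that T2 minus T1 also contains postnatal transition, recovery from hypoxia and changes in support, and that controls have no day 1/2 scan to separate these.

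The cost is wording and one standard analysis. No extra scans or infants are needed. The price in interpretation is that the change is reported as change over a period and not as a causal effect of warming.
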